## Abstract

**Background:**

Mobility scooters can facilitate community participation among individuals with mobility limitations. However, accidents are a serious concern with scooter use. Scooter training has been recommended to improve safety, but there are currently few validated programs available. Therefore, we developed a Systematic, Comprehensive, One-to-One Training (SCOOT) program for scooter users. We will conduct a study to evaluate the outcomes produced by the provision SCOOT.

**Methods:**

This feasibility study will use a mixed-methods, rater-blinded, randomized control trial, with a two-step wedge design. The study has two arms: an immediate intervention group, which will receive the intervention directly after baseline assessments, and a delayed intervention group, which will receive the intervention after a 6-week period. Forty participants, who will be stratified based on whether or not participants have previously held a driver’s license, will be randomly assigned to each arm. The intervention for this study consists of 6 weeks of one-to-one scooter training by an experienced occupational therapist, who will provide training once or twice per week over the 6 weeks. The primary outcome measure is subjective scooter skills, measured using the Wheelchair Skills Test for scooters. Secondary outcomes include objective scooter skills, confidence, mobility, and satisfaction with selected participation activities. Descriptive measures include cognitive status, functional status, hearing, vision, physical accessibility of the home and community, and visual attention and task switching. Qualitative interviews will be conducted with the first ten willing participants from each group to learn about their scooter use and experiences with SCOOT.

**Discussion:**

The results of this study will inform a larger randomized control trial. If the intervention is proven to be effective in this larger study, it may have important implications for policy and practice.

**Trial registration:**

ClinicalTrials.gov identifier: NCT02696213. Registered on 23 February 2016.

**Electronic supplementary material:**

The online version of this article (doi:10.1186/s13063-017-1963-y) contains supplementary material, which is available to authorized users.

## Background

Many people have disabilities that necessitate the use of powered mobility devices. Mobility scooters (i.e., three or four wheeled devices controlled by a tiller) may be preferred over power wheelchairs, as they are generally more affordable and perceived as less stigmatizing [1, 2]. Although the prevalence of scooter use has been increasing in North America [3, 4], scooter use appears to vary considerably in different countries. For example, it was estimated that 0.3% of Canadians used a scooter [4], whereas in Australia this figure was 1% [5].

Scooters, like many mobility devices, may be a mixed blessing [1]. Several studies have found that the provision of a mobility scooter is positively associated with feelings of independence, higher frequency of daily activities, and increased social participation [6–9]. However, scooter-related accidents (e.g., falls, collisions with stationary and moving objects) are a concern, as they can cause serious, sometimes fatal injuries to users and others [10, 11]. A wide spectrum of injury rates have been reported for scooter users (e.g., from 1.54 [12] to 15 [5] injuries per person per year). Similarly, a variety of accident rates have been reported for power wheelchair users (e.g., 5–18% of community dwelling users experience accidents each year [13]). To improve safety, scooter training has been recommended [14], which could include advanced skills such as navigating curbs and uneven surfaces, accessing public transit and elevators, and avoiding obstacles [15].

There are a variety of potential benefits of wheeled mobility skills training but few users report receiving formal training. Manual wheelchair training has been found to improve skills [13] and increase confidence [16]. However, most scooter users receive very little training, which may be attributed to limited accessibility. Two surveys found that a quarter of scooter users received training [5, 15]. Although there appears to be great variability in terms of the training provided [15], training appears to focus on rudimentary skills (e.g., basic operating skills, driving indoors and outdoors, transferring on and off the scooter), rather than more advanced skills such as crossing streets or using transportation [15].

Research on the efficacy of scooter training is limited. In a scoping review conducted by Mortenson and Kim [17], two small scale, randomized control trials (RCTs) were identified. One trial found that 3D virtual reality training in combination with conventional training produced similar improvements in scooter skills as conventional training alone. The second study found that scooter skills improved significantly with meta-cognitive training combined with on-road driving practice, compared to computerized cognitive training alone [18]. However, the validity of these findings are threatened by their small sample sizes, lack of non-intervention control arms, and use of non-validated outcome measures [17], such as the study-specific functional evaluation rating scale used in the study by Jannink et al. [19].

To improve the mobility and social participation of scooter users and to decrease safety concerns, we created a community-based training program built on the Wheelchair Skills Training Program [20] and feedback from Vancouver Coastal Health scooter prescribers, called Systematic, Comprehensive, One-to-One, Training (SCOOT) for scooters. We are conducting a study to explore the feasibility of a mixed-methods RCT, which will evaluate the efficacy of this intervention. Based on the typology of feasibility research [21], this study will focus on process assessment (i.e., recruitment rate, retention rate, treatment fidelity, adherence rate, suitability of the eligibility criteria and measures, and respondent burden) and on scientific assessment (i.e., safety of the intervention, reliability and validity of the measures with this population, estimates of the effect of the intervention and variances of the effects).

### Hypothesis

We anticipate that the feasibility outcomes will support a subsequent multi-site trial. We expect that our recruitment targets will be met, that > 90% treatment, > 80% adherence, and > 80% retentions will be obtained, that SCOOT will be as safe as non-intervention, and that participants will provide complete responses to > 90% of items from all measures.

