## Methods

### Study design

To conduct this exploratory, mixed-method, rater-blinded RCT, a two-step wedge design will be used, as illustrated in Fig. 1. With a step-wedge design, participants are randomly assigned to receive the same intervention at different times [22]. For this study, a total of 40 participants, stratified based on whether or not they have previously held an automobile driver’s license, will be randomly assigned to either the immediate intervention group or the delayed intervention group. As illustrated in Fig. 1, the immediate intervention group will receive the intervention after consent and baseline data have been collected, while the delayed group will receive the intervention after a 6-week delay. The primary endpoint of this study is at 6 weeks, so we can compare the effects of the intervention with the group who has yet to receive it.

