### Randomization

The allocation of each participant will be communicated to the study research coordinator after baseline data and consent have been obtained. The allocations will be managed by the study statistician using an auditable computer program and a 1:1 allocation ratio within each stratum. Blocking sizes will not be revealed until needed for analysis.

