### Procedure

The research coordinator and principal investigator will train raters to administer all study measures. This training will include review of manuals, observations of pre-recorded mock interviews and assessments with practice scoring, practice administration with other research staff with feedback provided, and video recording of practice administration for self-reflection.

Upon enrolment, participants will be provided with a unique ID number, and the researcher will obtain written consent prior to baseline testing with all participants. The immediate intervention group will receive SCOOT after their baseline testing once or twice per week over a 6-week period (varying from 9 to 18 hours total), while the delayed intervention group will receive SCOOT 6 weeks after baseline testing. Upon completion of the intervention, all participants will be re-assessed at 6, 12, 26, and 52 weeks after randomization. Participants will also be asked not to participate in any additional training until 12 weeks have elapsed. The intervention will be discontinued upon the participant’s request, or if they are unable to continue with the research due to unforeseen events (e.g., illness).

Measures will be administered in a random order to reduce order effects. All measures, except the Wheelchair Outcome Measure (WhOM), will be collected by a blinded research assistant. The WhOM will be administered by the study therapist as this will inform the intervention. During training sessions, the therapist delivering the intervention will record any adverse effects of the intervention such as falls. As suggested by Little et al. [24], to reduce missing data, we will stress, during the consent process and whenever there is contact between participants and study personnel, the importance of collecting measurement data for the duration of the study, especially for those who discontinue the intervention.

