##### Scooter use and incidents

Participants will be asked to keep a diary of any scooter-related adverse events, including the following: tips or falls from the scooter, injuries to self, accidental contact with others, injuries to others, and damage to property. Participants will be asked to record the number of hours per day that they use their scooters over the course of the study.

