As a feasibility study for a RCT, the research has several limitations. First, given the single-site nature of this research, new feasibility issues may arise in attempting to apply the results to additional sites; however, findings from our feasibility study should be able to help us anticipate many of these problems so that they can be addressed proactively. Secondly, the size of the current sample only allows for the detection of large effect sizes. Larger samples may be required to detect smaller effect sizes, which may occur with important secondary outcomes such as accidents and injuries.

In summary, given the limited research on scooter training, this feasibility study is needed to lay the groundwork for a larger RCT to evaluate whether our novel, community-based intervention improves mobility, social participation, and safety. If the results of this larger experimental study are positive, we will perform additional research evaluating the best way to deliver this intervention, e.g., mentorship or online training. Economic studies can be performed to conduct a cost-benefit analysis of the intervention in the future.

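### The expectation that SCOOT is as safe as no intervention has no margin and rests on about 2.3 person-years per arm, so it should be restated as estimation

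*Protocol article*

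**What the plan says.** The Hypothesis section opens by anticipating that the feasibility outcomes will support a later multi-site trial. It then lists expectations with numeric targets for treatment, adherence, retention and item completion. In the same list stands "that SCOOT will be as safe as non-intervention", with no margin, event definition, time window or confidence level. The Background also names safety of the intervention as part of the study's scientific assessment.

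The design fixes how much untrained time there is. Study design has "a total of 40 participants, stratified based on whether or not they have previously held an automobile driver’s license", Randomization gives "a 1:1 allocation ratio within each stratum", and "the delayed group will receive the intervention after a 6-week delay". After that both groups are trained.

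Incidents are collected in two ways. Under Scooter use and incidents, "Participants will be asked to keep a diary of any scooter-related adverse events", together with daily hours of use. Under Procedure, "During training sessions, the therapist delivering the intervention will record any adverse effects of the intervention such as falls". The Quantitative data section plans Poisson regression to obtain an effect size for counts such as accidents and falls.

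The Discussion looks to a larger trial to quantify adverse events. It concedes that "the size of the current sample only allows for the detection of large effect sizes" and that accidents and injuries may need larger samples.

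**The concern.** To say that one condition is as safe as another is an equivalence or non-inferiority claim. Such a claim needs a margin and enough events to exclude harm beyond it. Here it sits beside targets that 40 participants can answer, such as retention, and is offered as support for going on to a larger trial. The participants are aged 60 or over with at most one month of scooter experience in the past year, and the Background describes scooter accidents as sometimes fatal. If the interval for the rate ratio is wide, a result showing no clear difference could be read as confirming equal safety when it says little either way. The expectation also pulls against the Discussion, which treats adverse events as a matter for a larger sample.

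**Working it through.** **The plan's only power figure.** The Quantitative data section gives a detectable effect size of 0.46 at α = 0.05 and 80% power, for the primary and non-count outcomes. Read as Cohen's f (d = 0.92) with 20 per arm, it reproduces: power is 80.9%. No corresponding figure is given for safety.

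**Inputs.** 40 participants at 1:1, so 20 per arm (Study design, Randomization); 6 weeks of untrained comparison (Study design); injury rates from 1.54 to 15 per person per year (Background).

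**Person-time.** 20 × 6/52 = 2.31 person-years per arm.

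**Expected events per arm**, m = rate × 2.308:
- 1.54 per year: m = 3.55
- 15 per year: m = 34.6

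The Background also cites 5–18% of power wheelchair users having an accident each year. Taken as a rate, that gives only 0.12 to 0.42 events per arm, but it concerns another device and counts people, not events.

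**95% interval around a rate ratio of 1**, Poisson counts, factor = exp(1.96 × √(2/m)):
- m = 3.55: exp(1.96 × 0.750) = 4.35, so 0.23 to 4.35
- m = 34.6: exp(1.96 × 0.240) = 1.60, so 0.62 to 1.60

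**Power to detect a doubling** (exact conditional test, two-sided 0.05, pure Poisson):

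| Rate per person-year | Power |
|---|---|
| 1.54 | 12% |
| 5 | 44% |
| 6 | 52% |
| 10 | 77% |
| 15 | 92% |

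**Power to show non-inferiority** when the arms are equal, Φ(ln(margin)/√(2/m) − 1.96). The margins are assumed, because the protocol gives none:
- margin 1.5: 8% at 1.54 per year, 39% at 15 per year
- margin 2: 15% at 1.54 per year, 82% at 15 per year

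**Sensitivity of the most favourable case** (15 per year, margin 2, 82%). Power falls to 73% if only 80% of the person-time is contributed. With full person-time it falls to 56% or 41% under an assumed negative binomial dispersion of 0.5 or 1.

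**Using later follow-up.** Adding all time from trained participants (20 × 52/52 + 20 × 46/52 = 37.7 person-years) gives up the randomized comparison. It still leaves interval factors of 2.92 and 1.41, because untrained time stays at 2.31 person-years.

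**The case against.** The case for leaving the text alone has real substance.

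- *A doubling need not be missed.* A reader might infer that no difference is the likely finding even if incidents double. That holds only below about 6 events per person-year; at 15 per year power is 92% under pure Poisson. The protocol gives no dispersion figure from which to lower this.
- *The rates may be too low for the outcome.* They are injury rates. The diary also covers tips and falls, accidental contact with others and property damage, so total incidents may exceed injuries and the intervals would narrow.
- *It is tempting to say that equal safety cannot be established at all.* That depends on a margin nobody has stated. With a margin of 2 and 15 events per year, power would be 82% under pure Poisson.
- *No decision rule is stated.* The wording is an expectation. Nothing in the protocol says that a non-significant difference will count as equal safety, and the planned Poisson analysis is for an effect size, not an equivalence test.
- *Unequal recording is not shown to be an error.* In weeks 0 to 6 only the immediate group has a therapist noting events, so a reader might infer a biased comparison. But the diary, kept by all participants, is the named outcome, and nothing in the protocol pools therapist records with it. Pooling would count against SCOOT, but it is not proposed.

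All five points stand as limits on the concern. They do not supply a margin or more untrained person-time, and they do not reconcile the Hypothesis with the Discussion.

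**Conclusion.** The point holds as a mismatch between a stated expectation and what the study can show. With 2.31 person-years per arm and truly equal arms, a typical interval would leave open an increase of 60% (at 15 injuries per person-year) to more than fourfold (at 1.54). For an assumed margin of 1.5, non-inferiority power is at most 39% anywhere in the protocol's injury range. Only a margin as loose as 2, rates near 15 per year and no overdispersion together would give adequate power.

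The figures assume 20 per arm with full six-week follow-up, Poisson counts except where dispersion is stated, and injury rates standing in for diary incidents. A statistical analysis plan could add a margin but could not add person-time. The change is worth making because it affects what the study may conclude, but it is a change of wording and not a flaw in the design. The question of recording source is a minor safeguard only.

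**What to change.** Replace the safety expectation in the Hypothesis section with an estimation statement along these lines:

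> Diary-recorded incident rates per person-week and per scooter-hour in weeks 0 to 6 will be reported by group, with the rate ratio and its 95% confidence interval. No conclusion of equal safety will be drawn from this study.

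This agrees with the Discussion and with the planned Poisson analysis, and the diary already collects the hours of use. As a safeguard, state that the between-group comparison uses the diary, which both groups keep, and list events recorded by therapists during training separately.

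The cost is a sentence in the Hypothesis and one table. Sample size, visits and data collection stay as they are. The downside is giving up an equal-safety claim that the data are unlikely to support.

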### Objectives

#### Quantitative objective

To evaluate the outcomes produced by the provision of a comprehensive program of scooter training among older adults.

#### Qualitative objectives

To explore how this intervention is experienced by recipients and trainers and to understand how the intervention was implemented in context.

## Methods

### Study design

To conduct this exploratory, mixed-method, rater-blinded RCT, a two-step wedge design will be used, as illustrated in Fig. 1. With a step-wedge design, participants are randomly assigned to receive the same intervention at different times [22]. For this study, a total of 40 participants, stratified based on whether or not they have previously held an automobile driver’s license, will be randomly assigned to either the immediate intervention group or the delayed intervention group. As illustrated in Fig. 1, the immediate intervention group will receive the intervention after consent and baseline data have been collected, while the delayed group will receive the intervention after a 6-week delay. The primary endpoint of this study is at 6 weeks, so we can compare the effects of the intervention with the group who has yet to receive it.

**Fig. 1 Fig1:**
[figure not shown]
SPIRIT figure. *II* Immediate Intervention, *DI* Delayed Intervention, *WST* Wheelchair Skills Test for Scooters, *WST-Q* Wheelchair Skills Test – Questionnaire for Scooters, *WheelCon* Wheelchair Use Confidence Scale, *WhOM* Wheelchair Outcome Measure, *LSA* Life Space Assessment, *SUID* Scooter Use Incidents Diary, *SPAQ* Scooter Physical Accessibility Questionnaire, *MoCA* Montreal Cognitive Assessment, *HHIE* Hearing Handicap Inventory for the Elderly, *LLDI* Late Life Disability Index

### Randomization

The allocation of each participant will be communicated to the study research coordinator after baseline data and consent have been obtained. The allocations will be managed by the study statistician using an auditable computer program and a 1:1 allocation ratio within each stratum. Blocking sizes will not be revealed until needed for analysis.

### Ethics

Ethical approval for this study has been provided by the University of British Columbia (H15-09121) and by the Vancouver Coastal Health Authority (V15-09121). This study was funded through a grant from the Canadian Institute of Health Research (340545). This protocol paper has been written in accordance with the SPIRIT (Standard Protocol Items: Recommendations for Interventional Trials) guidelines (Additional file 1) [23]. Any modification of important protocol will be made through an ethics amendment with the institutional review board prior to implementing the given change.

### Participants

For this feasibility study we plan to recruit 40 participants. As the majority of wheeled mobility users are older adults [4], the eligible community dwelling participants for this study are (1) English-speaking adults, (2) aged ≥ 60 years, (3) have one month or less combined experience of using a scooter within the past year, and (4) are able to independently transfer in and out of a scooter. We have not defined the population of interest based on their diagnoses (e.g., stroke, spinal cord injury, Parkinson’s disease), because the use of a scooter is not diagnosis specific. Individuals who have cognitive impairments that will prevent them from providing consent and from reliably completing the study questionnaires, reside in a nursing home, or plan to move outside the study intervention delivery area within the next year will be excluded.

Participants will be recruited through a variety of sources, including community healthcare units, vendors, and various seniors’ groups and seniors’ centres. Participants will be recruited through these organizations via posters, presentations, social media, and referrals. Occupational therapy staff and vendors will invite eligible clients to consider the trial.

### Procedure

The research coordinator and principal investigator will train raters to administer all study measures. This training will include review of manuals, observations of pre-recorded mock interviews and assessments with practice scoring, practice administration with other research staff with feedback provided, and video recording of practice administration for self-reflection.

Upon enrolment, participants will be provided with a unique ID number, and the researcher will obtain written consent prior to baseline testing with all participants. The immediate intervention group will receive SCOOT after their baseline testing once or twice per week over a 6-week period (varying from 9 to 18 hours total), while the delayed intervention group will receive SCOOT 6 weeks after baseline testing. Upon completion of the intervention, all participants will be re-assessed at 6, 12, 26, and 52 weeks after randomization. Participants will also be asked not to participate in any additional training until 12 weeks have elapsed. The intervention will be discontinued upon the participant’s request, or if they are unable to continue with the research due to unforeseen events (e.g., illness).

Measures will be administered in a random order to reduce order effects. All measures, except the Wheelchair Outcome Measure (WhOM), will be collected by a blinded research assistant. The WhOM will be administered by the study therapist as this will inform the intervention. During training sessions, the therapist delivering the intervention will record any adverse effects of the intervention such as falls. As suggested by Little et al. [24], to reduce missing data, we will stress, during the consent process and whenever there is contact between participants and study personnel, the importance of collecting measurement data for the duration of the study, especially for those who discontinue the intervention.

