### Experimental intervention

SCOOT is a community-based, client-centered intervention that embeds skills training into social activities that users want to accomplish. It also uses trainer-facilitated problem solving to identify strategies to manage environmental barriers and to enable better user social participation. This intervention represents a departure from customary scooter training that is often very limited and which focuses on learning discrete skills outside of the user’s normal environment. With SCOOT, skill training (i.e., on driving, basic and advanced scooter skills) will take place during self-selected, home- or community-based activities that participants want to perform using their scooters. We will identify these activities using the WhOM [21], which identifies the most important home- and community-based activities participants wish to perform using their scooters (described below). The skills training component of the intervention is based on the scooter version of the Wheelchair Skills Training program [20].

The intervention will be held in the neighborhood of the participants, located in the Greater Vancouver Regions District of British Columbia, Canada. The intention of conducting the study within the neighborhood of the participant is to facilitate the transferability of training and to improve the ecological validity. In addition, training in the community aims to reduce participant burden of travelling to our research site, and to improve adherence. These neighborhoods are all located within an urban setting, and locations include, but are not limited to, community centers, grocery stores, and parks.

SCOOT for scooter mobility skills will be provided by occupational therapist trainers who will be trained by the principal investigator to use the same standardized approach. The therapist will keep a record of the skills that they have taught and hours of training provided. During training sessions, the therapist delivering the intervention will record any adverse effects of the intervention such as falls. We will collect data on the number of therapist visits, length of visits, therapist years of practice, years of experience working in this area, and therapist qualifications.

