##### Satisfaction with participation in selected activities

The WhOM is a participant-specific tool that evaluates satisfaction with participant-identified home and community activities associated with wheeled-mobility provision using an 11-point scale (0 = completely unsatisfied to 10 = completely satisfied) [21]. A mean satisfaction score is calculated by dividing the sum of all satisfaction scores by the number of goals. The WhOM demonstrates promising psychometric properties among community-dwelling, power-mobility users with good 2-week test-retest reliability (ICC = 0.91 for the mean satisfaction score) [27] and moderate correlations with other measures of social participation and device satisfaction [28].

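### The therapist, not the blinded assistant, collects the WhOM satisfaction ratings, so the 6-week effect estimate for this secondary outcome may include an avoidable courtesy component aligned with allocation

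*Protocol article*

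**What the plan says.** The Procedure section states the general rule and its one exception: "All measures, except the Wheelchair Outcome Measure (WhOM), will be collected by a blinded research assistant". The next sentence gives the reason: "The WhOM will be administered by the study therapist as this will inform the intervention". The same section schedules re-assessment of all participants at 6, 12, 26 and 52 weeks after randomisation.

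The WhOM has two roles in this trial.

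- **Input to training.** Under Experimental intervention, training is built around activities the participant selects: "We will identify these activities using the WhOM [21". The same section says who trains: "SCOOT for scooter mobility skills will be provided by occupational therapist trainers".
- **Outcome.** The abstract lists it: "Secondary outcomes include objective scooter skills, confidence, mobility, and satisfaction with selected participation activities". The section on satisfaction with participation describes a "participant-specific tool that evaluates satisfaction with participant-identified home and community activities", scored "using an 11-point scale (0 = completely unsatisfied to 10 = completely satisfied" and averaged over the participant's goals.

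The abstract describes the trial as a "mixed-methods, rater-blinded, randomized control trial", with no qualification for the WhOM. Study design sets the primary endpoint at 6 weeks, when one arm has been trained and the other has not. The limitations in the Discussion do not mention how the WhOM is collected.

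**The concern.** The reason given covers only the first of the two roles. A therapist needs to know which activities matter to the participant before training starts. Nothing in that need requires the therapist to record how satisfied the participant is with those activities afterwards.

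The stake is the 6-week comparison. A participant in the immediate arm has just finished 9 to 18 hours of one-to-one training and would give a satisfaction score to a therapist involved in it. A participant in the delayed arm would give the score to a therapist who has not yet trained them. The form is the same but the social setting differs, and it differs exactly by allocated arm. Randomisation does not balance this, and adjustment for the baseline score does not remove it, because it arises after baseline.

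The study lists estimates of the intervention effect and of its variance among its aims (Background), and the Analysis section will compute effect sizes for the non-count secondary outcomes. An inflated WhOM effect could therefore enter the planning of the larger trial, and the collection procedure could be copied with it.

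**Working it through.** **1. Does the stated reason apply at each assessment?**

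| Assessment | Immediate arm | Delayed arm | Can the rating inform training? | Arms differ in relation to the therapist? |
|---|---|---|---|---|
| Baseline | before training | before training | yes, both arms | no |
| 6 weeks | just trained | about to be trained | delayed arm only | **yes** |
| 12 weeks | trained earlier | just trained | no | only in recency of training |
| 26 and 52 weeks | trained | trained | no | little |

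The reason holds at baseline, and at 6 weeks for the delayed arm. The trained-versus-untrained asymmetry is confined to 6 weeks, which is the comparison the trial is designed around.

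**2. What is inferred rather than stated?** The Procedure section says study therapist. That this is a trainer delivering SCOOT follows from the reason given and from Experimental intervention. That it is each participant's own trainer is likely but not stated. The assessment schedule is in Fig. 1, which is not available here. The general re-assessment sentence makes WhOM follow-up ratings probable.

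**3. The plan's own detectable effect, as a yardstick.** The Analysis section gives 0.46 for 40 participants, α = 0.05 and 80% power, without naming the metric or the sidedness.

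- Read as Cohen's f in a two-group analysis of covariance with one covariate: noncentrality = f² × N = 0.46² × 40 = 8.46 on 1 and 37 degrees of freedom, power 0.809. The stated figure is reproduced.
- Read as Cohen's d with 20 per arm, power would be 0.29 two-sided or 0.41 one-sided, so f is the reading that fits.
- For two equal groups d = 2f = 2 × 0.46 = 0.92.

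**4. Illustration of size (assumed inputs).** The documents give no WhOM SD and no size of courtesy bias. I assume an SD of 1.5 to 2.5 points, a shift of 0.5 or 1.0 point in the immediate arm only, no true effect, 20 per arm and an unadjusted two-sided t-test at 5%. Spurious d = shift / SD, and noncentrality = d × √(20/2).

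| Shift | SD | Spurious d | Chance of a significant result favouring training |
|---|---|---|---|
| 0.5 | 2.5 | 0.20 | 9% |
| 0.5 | 2.0 | 0.25 | 12% |
| 0.5 | 1.5 | 0.33 | 18% |
| 1.0 | 2.5 | 0.40 | 23% |
| 1.0 | 2.0 | 0.50 | 34% |
| 1.0 | 1.5 | 0.67 | 54% |

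Without bias the chance in that direction is 2.5%. Against d = 0.92 the spurious effect is 0.20/0.92 = 22% to 0.67/0.92 = 73% of what the trial is sized to detect. With a shift of zero, which the documents do not exclude, there is no distortion. The table shows only that a modest shift on this scale would matter.

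**The case against.** The strongest defence has four parts.

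- **The exception is open and reasoned.** A reader might infer that the plan contradicts its own rater-blinded label. It does not: the Procedure section states the exception and explains it. This is a design weakness, and the label needs a qualifier.
- **The therapist does not score.** The participant gives the rating and knows whether training has taken place. A blinded interviewer would remove the wish to please the trainer but not expectancy. The primary outcome, perceived capacity scored by the participant, carries the same residual. This stands, and it limits what any fix can achieve. The courtesy part is still avoidable, and the plan already uses the blinded assistant for its other self-report scales.
- **Little hangs on it.** A reader might infer that the trial's conclusions are at risk. The documents do not support that. The WhOM is one of several secondary outcomes in a feasibility study of 40. The expectations set out under Hypothesis concern recruitment, treatment delivery, adherence, retention, safety and completeness of responses, and none uses a WhOM contrast.
- **Blinded collection has its own risk.** Talking about trained activities could reveal allocation to the assistant, who also administers the objective skills test, and measures are given in random order. This stands and shapes the fix.

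A reader might also extend the arm difference to all four follow-ups. By 12 weeks both arms have been trained, so the documents support it only at 6 weeks.

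**Conclusion.** The point holds as a moderate recommendation; it is not a condition for the study to proceed. The plan leaves the satisfaction ratings of a secondary outcome with an unblinded therapist for a reason that covers only the choice of activities. At 6 weeks this may add to the WhOM effect estimate a courtesy component that follows allocation.

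The conclusion rests on two readings: that the study therapist is a SCOOT trainer, and that the WhOM is rated at the general re-assessment times. The size of the bias cannot be derived from the documents. The range of 0.20 to 0.67 standard deviations depends wholly on the assumed SD and shift. The primary outcome and the feasibility criteria are not affected.

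**What to change.** Separate the two roles of the WhOM.

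1. The activity list is fixed before training. The therapist elicits it, or receives it from whoever does, and uses it to plan the sessions.
2. The blinded assistant records the 0-10 satisfaction ratings on that fixed list at baseline and at 6, 12, 26 and 52 weeks. Including baseline keeps the type of interviewer the same on both sides of the baseline-adjusted analysis.
3. At each visit the ratings come after the rater-scored objective skills test, so that talk of trained activities cannot unblind that test.

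The cost is a change to the Procedure wording, a short addition to the assistant's existing visit, a handover of the list, and a small restriction on the random order of measures. No extra staff or visits are needed.

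If the therapist must keep collecting the ratings, report the WhOM as an unblinded outcome, qualify the rater-blinded label accordingly, and add the point to the limitations, so that the larger trial does not take the effect size at face value.
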